**Admission criteria:**

**Children from 6 to 59 months for which the P/T<70% or MUAC <110 mm**

**Check for complications and do the appetites test**

**Children with complication and/or failing appetite test.**

1. Bilateral pitting oedema grade 3*(severe oedema)

OR

2. MUAC<110 mm AND bilateral pitting oedema grades 1 or 2 (marasmic kwashiorkor)

OR

3. MUAC<125 mm OR bilateral pitting oedema grades 1 or 2

AND one of the following:

Anorexia

Lower respiratory tract infection

Severe palmer pallor

High fever

Severe dehydration

Fails appetite

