**Phase 2 outpatient treatments in the primary health center**

All children with severe acute malnutrition without medical complications and that have passed the [appetite test](http://motherchildnutrition.org/malnutrition-management/info/appetite-test.html) can go directly to Phase 2.

Children that are admitted directly to Phase 2 as out-patients should be provided with a systematic medical examination and given routine medicine.

Children transferred from [in-patient treatment](http://motherchildnutrition.org/malnutrition-management/management-severe-acute-malnutrition/in-patient-treatment-phase-2.html) should be registered as "transferred from".

Surveillance of the children:

- Every week, weight will measure, entered and plotted on the Child Card.
- Every week, the presence of bilateral [oedema](http://motherchildnutrition.org/early-malnutrition-detection/detection-referral-children-with-acute-malnutrition/screening-for-acute-malnutrition.html" \l "Bilateral pitting oedema) will assess and noted in the Child Card.
- Every week, body temperature is measured and noted in the Child Card.
- Every week, standard clinical signs (stool, vomiting, dehydration, cough, respiration and liver size) will assessed and noted in the Child Card.
- Every week, [Mid-Upper Arm Circumference (MUAC)](http://motherchildnutrition.org/early-malnutrition-detection/detection-referral-children-with-acute-malnutrition/screening-for-acute-malnutrition.html" \l "Mid-upper Arm Circumference (MUAC)) will take.
- Every month measurement of height/length

**RUTF** is provided as take-home therapeutic food for malnourished children only.

- The amount of RUTF provided to the caregiver will base on the class of weight and on the necessary quantity required to last until the next visit to the out-patient site.
- Use the RUTF Feeding Table
- Breastfeeding children will always give Breast-Milk before RUTF.
- Move the child in phase 1 (in-patient)
- If the child develops any medical complications that demand in-patient treatment
- If the child has severely reduced appetite
- If the child increases/develops oedema
- If the child develops “refeeding diarrhoea” sufficient to lead to weight loss,
- If the child does not respond to the treatment
- If there is a weight loss for 2 consecutive weighing sessions
- If there is a weight loss of more than 5% of body weight at any visit,
- If the weight stays for three consecutive weighing sessions.

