**Ensuring ambulatory care for moderately malnourished children**

All case of moderate acute malnutrition (70 %< W/H <80%) will enter in an ambulatory program emphasizing an appropriate child-centered counselling on feeding practice and care. Home visits will be made once a week to assess feeding practices and child specifics problems, and needs. Although following the main recommendations reported in table 3, the rehabilitation will be thus tailored to each case. Two important aspects will be stressed: frequency and energy density of meals. Means to improve these two aspects will be defined in accounting for the purchase power and the food accessibility of each family. Families will be encouraged to use local foods, e.g. add 5 ml of oil in the gruel ration and provide the child with snacks several times during the day. RTUF could be purchased at the health centre. The follow-up of the nutritional status will be made once a week in the health centre. During every visit the anthropometric measures will be taken (weight height, MUAC) to follow the evolution and the presence of other diseases will be assessed for providing adequate treatment.

A child will be confirmed cured when his/her W/H>80% and growth curve ascending for two consecutive weighing (2 consecutive weeks).

A particular attention will be paid to children not responding to the programme in order to adapt rapidly and adequately the management. Children who have not gained weight after two weeks of follow-up will be thoroughly examined to assess the presence of chronic pathologies (cardiac malformation, renal deficiency, HIV infection, pulmonary tuberculosis) and begin an adequate treatment, if possible. If a chronic pathology is ruled out, the family will be encouraged to use RTUF. Children who developed a medical complication and/or loose weight will be transferred to the hospital.

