**Children with appetite, and no complication.**

1. MUAC<110 mm

OR

2. Bilateral pitting oedema grades 1 or 2 with MUAC>110 mm

AND

Appetite

Clinically well

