**Phase 2 Out-patient therapeutic care**

**RUTF follow-up in the primary health facilities**

**Fails appetite or develops medical complication.**

Phase 1: inpatient care in the district hospital

IMCI / WHO protocols

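### Section 3.3.4 places an uncomplicated child aged 6-59 months with W/H 70-80% and MUAC<110 mm under two different treatment rules and does not say which prevails

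*Protocol*

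**What the plan says.** All the rules are in protocol section 3.3.4, Improving the Structural dimension.

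- **Definition of severe malnutrition** (Upgrading the reference hospital paediatric services): W/H<70% or bilateral oedema. MUAC is not part of it. Severe cases, and moderate cases with complications, enter the two-phase inpatient and outpatient programme.
- **Moderate malnutrition** (Ensuring ambulatory care for moderately malnourished children): "All case of moderate acute malnutrition (70 %< W/H <80%) will enter in an ambulatory program". Care consists of tailored feeding counselling, local foods, weekly home visits and weekly follow-up at the health centre. On RUTF, the section says "RTUF could be purchased at the health centre". The family is encouraged to use it if the child has not gained weight after two weeks and chronic pathology has been ruled out.
- **Chart entry line** (Admission criteria): "Children from 6 to 59 months for which the P/T<70% or MUAC <110 mm". P/T is read here as weight-for-height; the main point does not depend on that reading.
- **Chart, outpatient box**, headed "Children with appetite, and no complication": item 1 is MUAC<110 mm and item 2 is "Bilateral pitting oedema grades 1 or 2 with MUAC>110 mm", in a child with appetite who is clinically well. The destination is Phase 2 care, described as "RUTF follow-up in the primary health facilities".
- **Phase 2 text** (Phase 2 outpatient treatments in the primary health center): direct entry is for "All children with severe acute malnutrition without medical complications and that have passed the" appetite test. RUTF "is provided as take-home therapeutic food for malnourished children only".

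**The concern.** The text classifies children by weight-for-height and oedema; the chart adds MUAC. The two measures need not agree in the same child, so a child can be moderate by the text and still be admitted to therapeutic care by the chart.

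Staff will meet this case with both measurements in hand. Under section 3.3.3, community health workers screen by MUAC and refer children below 12.5 cm. The moderate programme then measures weight, height and MUAC at every visit. Under section 3.4, health workers are to be trained on prescribing RUTF.

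At stake is the care of that child: enrolment in Phase 2 therapeutic care with RUTF supplied, or counselling with RUTF that the family may buy. Two health centres could each follow the protocol and treat the same child differently. The moderate programme also declares cure on W/H>80% with a rising growth curve and sets no MUAC condition, so a child could be discharged as cured while still meeting the chart's entry line.

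**Working it through.** The plan gives no figure to reproduce. The check is logical: take one child through each rule as written.

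**Test child:** age 6-59 months, W/H 75%, MUAC 105 mm, no oedema, good appetite, no complication.

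| Rule in section 3.3.4 | Test | Result |
| --- | --- | --- |
| Text definition of severe | W/H<70%? No. Oedema? No. | Not severe |
| Moderate programme | 70%<75%<80%? Yes. MUAC exclusion? None stated. | Ambulatory counselling, RUTF for purchase |
| Chart entry line | MUAC 105<110 mm? Yes. | Admitted |
| Outpatient box, item 1 | MUAC<110 mm, appetite, clinically well? Yes. | Phase 2 |
| Chart destination and Phase 2 text | Phase 2 care | RUTF follow-up, RUTF provided |

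The Phase 2 text does not capture this child by itself, because it speaks of severe acute malnutrition and the text definition of severe has no MUAC criterion. The child enters through the chart; the Phase 2 text only says how RUTF is supplied there.

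**How many profiles behave this way.** The rules were run over W/H (65, 75, 85%) x MUAC (105, 110, 118, 130 mm) x oedema (none, grade 1, grade 3) x complication or failed appetite (no, yes), that is 3 x 4 x 3 x 2 = 72 profiles. Among children whom the text does not call severe, exactly one uncomplicated profile falls under both the moderate programme and the outpatient box: W/H 75%, MUAC 105 mm, no oedema. The result is the same if the chart is read by its entry line and box heading instead of its numbered items. The count describes the grid and says nothing about how common such children are.

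**Chart wording, compared with the text definition.** These points show no clearly different treatment:

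- The entry line omits bilateral oedema, which the definition counts as severe and both boxes use.
- Inpatient item 3 accepts MUAC<125 mm with a complication, which is wider than the entry line. The text already admits moderate cases with complications.
- No numbered item lists W/H<70%, although the entry line does. These children can still be routed by the box headings and the Phase 2 text.
- Apathy is a complication only in the text, and high fever only in the chart.

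**The case against.** **The chart could be taken to prevail.** It carries the admission criteria, joins its two tests with an or, and is labelled as the decision schema. On that reading MUAC<110 mm admits the child whatever the W/H, and the moderate programme takes the rest. This is probably the intention. But the moderate rule claims all cases in its W/H range, and the definition that could take this child out of it lacks MUAC. The reading has to be supplied by the reader, so the point stands.

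**The RUTF contrast can be overdrawn.** A reader might infer free RUTF against RUTF for purchase only. The documents do not support that: Phase 2 RUTF is provided, with no price terms stated, and the moderate text does not say only. The moderate programme also has weekly follow-up and transfer to hospital on weight loss or complication. What remains is two different programmes with different stated access to RUTF.

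**Oedema.** A reader might infer a second conflict for a well child with MUAC<110 mm and grade 1-2 oedema, since inpatient item 2 and outpatient item 1 can both be met. This arises only if outpatient item 1 is read alone. Inpatient item 2 names that exact combination, and outpatient item 2 confines oedema to MUAC above 110 mm, so inpatient care is evidently meant.

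**Extraction.** The chart's arrows and box nesting were lost in reading the PDF, so some and/or grouping is uncertain. The main conflict rests on single intact lines and does not depend on the layout. The points about chart wording are treated as tidying partly for this reason.

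**Conclusion.** The conflict holds for one profile: age 6-59 months, W/H 70-80%, MUAC<110 mm, no oedema, good appetite, no complication. Below 6 months the chart does not apply and there is no conflict.

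The severity is modest. This is an ambiguity in care delivery and patient safety, and the risk lies mainly on one side: the moderate rule, followed literally, gives less intensive care to a child whom the chart admits to therapeutic care. The documents give no joint distribution of W/H and MUAC, so the number of children cannot be stated.

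A reader might infer that the trial's results are put in doubt. The documents do not support that. The wasting outcome in section 3.5 is a weight-for-height Z score of -2 or below in children aged 0-24 months, and neither it nor the 180 children per cluster uses these placement rules.

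**What to change.** **Main change.** Add MUAC<110 mm (age 6-59 months) to the definition of severe malnutrition, beside W/H<70% and bilateral oedema. Limit the moderate programme to children who do not meet that definition.

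**Tidying of the chart, to be checked against its original layout.**

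- Add bilateral oedema, and moderate malnutrition with complications, to the entry line so that it matches the definition and inpatient item 3.
- List W/H<70% in the boxes. In inpatient item 3, W/H<80% with a complication covers both severe and moderate cases.
- State that the outpatient items for MUAC<110 mm and W/H<70% exclude grade 3 oedema and MUAC<110 mm with grade 1-2 oedema, which go to inpatient care as inpatient items 1 and 2 already intend. Without this exclusion, adding W/H<70% to the outpatient box would itself create a double placement. Repeat the exclusion in the Phase 2 entry sentence.
- Use one list of complications in the text and the chart.

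**Check of the new wording.** Over W/H (<70, 70-80, >80%) x MUAC (<110, 110-124, 125 mm or more) x oedema (none, grade 1-2, grade 3) x complication (no, yes), that is 3 x 3 x 3 x 2 = 54 profiles, none has two placements and 51 have exactly one. The remaining 54 - 51 = 3 have W/H>80% and no oedema, and section 3.3.4 sets no placement for them: MUAC 110-124 mm uncomplicated, and MUAC 125 mm or more with or without a complication. They lie outside this point.

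**Cost.** Protocol, chart and job-aid wording before training, with the clinical team confirming the cut-offs. Outcomes, sampling and sample size do not change.

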**Children with appetite, and no complication.**

1. MUAC<110 mm

OR

2. Bilateral pitting oedema grades 1 or 2 with MUAC>110 mm

AND

Appetite

Clinically well

**Phase 2 Out-patient therapeutic care**

**RUTF follow-up in the primary health facilities**

**Fails appetite or develops medical complication.**

Phase 1: inpatient care in the district hospital

IMCI / WHO protocols

**Return of appetite and reduction of oedema**

Transition phase

In-patient with RUTF

Discharge to follow up

Schema for the decision making process

## The intervention implementation process

The intervention will be integrated to usual activities addressing to young children in the health facilities. Delivery of the intervention will be monitor, by the local health team at routine monthly review meetings. The investigators role will be restricted to the measurement of outcomes.

* At the national and regional level:

A workshop will be organized by the project team to present the project, to the head of the ministry of health and his partners (UNICEF, WHO NGO…). The main objective is to obtain their adhesion and accompaniment, and the utilization of the result in the national level.

* On the level of the medical district of Houndé: A local workshop will be organized by the project team; during which the project will be presented. Will be invited to this workshop: the district team, the local authority and health centre committee management, the social actors, the communities’ heads, the local NGO and women associations, the partner of development… The objective is to obtain their adhesion and their accompaniment.

* On the level of the primary health centers: four strategies of installation are considered:

1) *Information of the health workers on the result of the baseline, the extent and the importance of* the nutritional problems, the effects of malnutrition on children health, their growth and their development.

*2) A basic training on IMCI modules,* the nutritional needs for pre-school children, to *the nutrition counseling*, to the interpersonal communication, in the patient centered approach, to a better control of the techniques of weighing and measurement of the children, the prescription and the regulation of the RUTF.

*3)*  Setting up a nutrition team in each health centre composed of the community health workers and the play leaders and two health workers. This team will undertake the execution of the activities envisaged in the protocol and the adaptation of this one to the local context, by taking account of opportunities and obstacles present. The methodology of work of this group will consist in following the cycle of research action , which is in fact a process of continuous training. Indeed, the methodology of research action answers well the need for continuous adaptation of the theoretical and scientific bases to the real context, and takes account of the importance to develop the autonomy of the health professionals in their capacity of adaptation.

4) Setting up of the accreditation committee and the audit team.

## Population and sample size

This study concerns all the health workers in the primary health facilities of the Houndé district and the children from 0 to 24 months as well as their mother or caretakers. The intervention unit is the health center and the population living in its catchment area, i.e. health centers will be randomized.

For the evaluation as well of the efficiency as of the impact of this intervention, the statistical unit will be consisted the center of health and its population of cover. On the level of each statistical unit, three types of samples will be necessary in comparison with the study populations:

- Health workers

A random sample of one health worker will be made by center.

*Inclusion criteria*: Personnel of health having at least one year of activity in the center.

Caregivers

Insofar as several outcomes used to compare the two groups of mother, the principal outcome used to compare the two groups, will be the proportion of caregivers having a good score of Knowledge on adequate breastfeeding and complementary feeding practices.

Several hypothesis have been considered to estimate the sample size. The reference method for the sample size calculation is the paper of Hayes et al for cluster design; we used equation N°4 of this paper

C=number of pairs=6 in our case Km = intracluster correlation coefficient; in the case of paired groups, 0, 25 is used as conservatory value.

= proportion of caregivers with a good score of Knowledge in the control group

= proportion of caregivers with a good score of Knowledge in the intervention group

n=sample size by cluster

The value of C being known in our case, we deduced from this equation, the values of n, according to several assumptions on the rate of caregivers with good knowledge and practices on breastfeeding and complementary feeding and according to two levels of power 1-β=0,80 or 0,90. This is shown in the table below.

**Estimate of the number of caregivers** necessary to compare the two groups

| = 0,25 | α=0,05  1-β=0,80 | α=0,05  1-β=0,90 |
| --- | --- | --- |
|  | n=15 | n=50 |
|  | n=33 | n=95 |
|  | n=11 | 20 |

By taking a maximum power, a sample of 95 women per cluster will be necessary, which is 1140 women in total.

*Inclusion criteria*: all women of childbearing age having a child into care from 0 to 59 months and living in the health center catchment area for at least one year at the time of the survey.

Children from 0 to 24 months

Taking into account the duration of the intervention a notable change on the child nutritional status could be measured at the level of wasting; which is relevant to measure in children 0 to 24 months. The primary outcome, to compare the two groups will be the proportion of wasted children that is to say the proportion of children with weight for height Z score ≤ -2. According to the baseline data, this proportion was 16.4 on average in the district. The same equation cited above was used to estimate the number of required children. We considered the hypothesis that, after the intervention, the proportion of wasted children would decrease from 16.4% to 10% in the intervention area. Considering two levels of power the numbers of required children is summarized in the table below.

Table IV: Estimate of the number of children necessary to compare the two groups

| = 0,25 | α=0,05  1-β=0,80 | α=0,05  1-β=0,90 |
| --- | --- | --- |
|  | n=180 | n=650 |

We also considered other values of:

| = 0,20 | α=0,05  1-β=0,80 | α=0,05  1-β=0,90 |
| --- | --- | --- |
|  | n=115 | n=200 |

| = 0,30 | α=0,05  1-β=0,80 | α=0,05  1-β=0,90 |
| --- | --- | --- |
|  | n=800 | n=5000 |

We finally kept our first hypothesis with = 0.25, 1-β = 0.80 which gives n = 180 (180 children per cluster).

I*nclusion criteria*: all children 0 to 24 months whose parents residing in the health center catchment area for at least one year at the time of the survey.

The selection of women and children will be in population and randomly. In contrast, the number of children required (180 by cluster) being greater than the number of women (95 per cluster), and to be more operational, we will choose to include in the study women of childbearing age with at least a child under 24 months. This will allow us to select our two populations at the same time.

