***Targets***

*Outcomes:*

- To reduce morbidity rate in under five children

- To reduce wasting rate in consulting children by 50% (from 16% to 8%)

- To reduce the annual incidence of severe malnutrition by 50%

- To reduce the cost of severe malnutrition care

-*Processes:*

- To improve communication and management skills of primary health workers, particularly in the domain of nutrition, by 100% (all mothers should be advised about exclusive breastfeeding and complementary feeding, instead of the current 24%; all sick children should have their weight and length/height measured at any consultation; all mothers of sick children should be asked and advised about feeding practices)

- To improve knowledge and feeding practices of caretakers by 50% (75% of the mothers will give the colostrums to the newborn; 60% of the mothers will practice exclusive breastfeeding)

- To manage cases of severe acute malnutrition in each health facilities

- To manage cases of severe acute malnutrition in line with international recommendations of good practice.

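### The clustering input of 0.25 is called an intracluster correlation, but the printed sample sizes rule that out; read as a coefficient of variation it fits their pattern, yet still does not give 80% power for wasting

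*Protocol*

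**What the plan says.** Section 3.5 (Population and sample size) takes its method from a cited paper on sample size for cluster-randomized trials: "we used equation N°4 of this paper". The inputs are "C=number of pairs=6 in our case" and a clustering parameter described as "Km = intracluster correlation coefficient; in the case of paired groups, 0, 25 is used as conservatory value".

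The caregiver table has three rows of n per cluster, for 80% and 90% power: 15 and 50, 33 and 95, 11 and 20.

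For the children, "The same equation cited above was used to estimate the number of required children". The planning hypothesis is that "the proportion of wasted children would decrease from 16.4% to 10% in the intervention area". The printed n per cluster at 80% and 90% power are 180 and 650 with the parameter at 0.25, 115 and 200 at 0.20, and 800 and 5000 at 0.30. The choice is then stated: "We finally kept our first hypothesis with = 0.25, 1-β = 0.80 which gives n = 180 (180 children per cluster".

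The equation, its symbols and the caregiver proportions are not visible in the text available. That is a loss in extraction and is not held against the plan.

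**The concern.** An ICC of 0.25 and a between-cluster coefficient of variation of 0.25 are very different assumptions. At 16.4% wasting, an ICC of 0.25 means a standard deviation between health centres of √(0.25 × 0.164 × 0.836) = 0.185, or 18.5 percentage points, which is larger than the mean itself. A coefficient of variation of 0.25 means 0.25 × 16.4 = 4.1 points.

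If the calculation used the second and the text names the first, the protocol claims to have allowed for far more clustering than it did. The Data analysis section plans mixed models for all analyses, and these can yield an ICC. A reader who set such an estimate, or one from the 2008 baseline survey, against 0.25 would see a wide margin, even if clustering were several times what the calculation allows.

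**Working it through.** **Inputs.** From section 3.5: 6 pairs, α = 0.05, p₀ = 0.164, p₁ = 0.10, n = 180, and the table entries above. Assumptions: two-sided α (sidedness is not stated), the lost symbol in the tables is Km, and the standard matched-pair form

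c = a + f × V / (p₀ − p₁)², with f = (z for α/2 + z for power)²,

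where a is the small-sample term (2 in the matched form; 1 and 0 also tried). f is 7.849 at 80% and 10.507 at 90%. Write S = p₀(1 − p₀) + p₁(1 − p₁) and Q = p₀² + p₁². For 16.4% versus 10%, S = 0.1371 + 0.0900 = 0.2271 and Q = 0.0269 + 0.0100 = 0.0369.

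- ICC reading: V = S × [ρ + (1 − ρ)/n]
- Coefficient-of-variation reading: V = S/n + k²Q

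**Step 1: can 0.25 be an ICC?** With pairs and rates fixed, V must fall between the two power columns by 10.507/7.849 = 1.339 (1.385 one-sided). Under an ICC, S cancels, so the test needs neither the missing rates nor the value of a.

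| Row | ρ + (1 − ρ)/n at 80% | at 90% | Ratio |
|---|---|---|---|
| Caregivers 15, 50 | 0.3000 | 0.2650 | 1.13 |
| Caregivers 33, 95 | 0.2727 | 0.2579 | 1.06 |
| Caregivers 11, 20 | 0.3182 | 0.2875 | 1.11 |
| Children 180, 650 | 0.2542 | 0.2512 | 1.01 |

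None is near 1.339. For 16.4% versus 10%, even unlimited children per cluster would need 7.849 × 0.2271 × 0.25 / 0.064² ≈ 109 pairs before adding a. At n = 180, V = 0.2271 × 0.2542 = 0.0577, and power is Φ(√(4 × 0.004096/0.0577) − 1.96) = Φ(−1.43) ≈ 8% (about 10% with a = 0).

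**Step 2: does a coefficient of variation fit the pattern?** The same ratio test on the children's table, at the stated rates:

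- k = 0.25: (0.2271/180 + 0.0625 × 0.0369) / (0.2271/650 + 0.0625 × 0.0369) = 0.003568/0.002655 = 1.34
- k = 0.20: 0.003451/0.002611 = 1.32
- k = 0.30: 0.003605/0.003366 = 1.07

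The first two rows fit; the third (800 and 5000) does not. The caregiver rates are missing, so only consistency can be shown: with 6 pairs and a = 2, 26% versus 52% gives 33 and 96 (printed 33, 95), and 39% versus 77% gives 15 and 49 (printed 15, 50). These rates were chosen to fit.

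**Step 3: what ICC does 0.25 then imply?** ρ = k² × p/(1 − p).

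- At 16.4%: 0.0625 × 0.164/0.836 = 0.0123, so 0.25 is 20.4 times larger.
- At 10%: 0.0625 × 0.10/0.90 = 0.0069, so 36 times larger.

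The design effect at n = 180 is 1 + 179 × 0.25 = 45.75, against 1 + 179 × 0.0123 ≈ 3.2.

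**Step 4: does the new reading return n = 180?** Solve n = S / [(6 − a)(0.064)²/7.849 − k²Q], with k²Q = 0.002306.

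| a | First term | n for 80% | Power at n = 180 |
|---|---|---|---|
| 2 | 0.002087 | no finite n | 57% |
| 1 | 0.002609 | 749 | 67% |
| 0 | 0.003131 | 275 | 75% |

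With a = 2, n = 180 would need 2 + 7.849 × 0.003568/0.004096 = 8.8 pairs. A larger effect comes closer to the print. In the printed order (0.25, 0.20, 0.30; 80% then 90%), against 180, 650, 115, 200, 800, 5000:

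- 16.4% versus 8.4%: 188, 681, 112, 199, 1039, no finite n
- 16% versus 8%, the target in the Objectives section: 165, 477, 105, 180, 545, no finite n

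**The case against.** The best defence is that this is a slip of terminology. No sample size appears to have been computed from an ICC of 0.25, so changing the label alters no child count, and section 3.5 already varies the parameter from 0.20 to 0.30. No section commits anyone to comparing a fitted ICC with 0.25, so the harm is a risk of misreading. All of that stands, and it keeps the point at the level of a correction to the text.

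It also stands that the case for a coefficient of variation is indirect. The equation is not visible, the caregiver rates are back-fitted, and for wasting, the one comparison whose rates survive, that reading does not return 180 two-sided in any variant. A reader might infer that the tables can only have come from a coefficient of variation. The documents do not support that: of the two readings it is the only one that fits the pattern, but it does not reproduce the children's table.

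The defence does not rescue the label. The ratio test uses only the protocol's own numbers, and every row fails it under an ICC, one-sided or two-sided. Nor is the point purely verbal, because correcting the name alone would leave an 80% power claim that the corrected formula does not bear out.

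**Conclusion.** The point holds. The value 0.25 is wrongly described as an intracluster correlation, and this conclusion depends on neither the missing equation nor the missing rates. Under the standard matched-pair form, which is an assumption, the tables behave as if 0.25 were a within-pair coefficient of variation. The equivalent ICC is about 0.012 at 16.4% wasting and 0.007 at 10%, so the stated value is about 20 times too large on the ICC scale at the control rate. The document offers no figure showing that 0.25 is conservative on either scale.

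Separately, with 16.4% versus 10%, 6 pairs and two-sided α, 180 children per cluster give about 57% power, or about 75% if the small-sample term is dropped, against the 80% claimed. The printed table sits closer to a fall to about 8%. Whether effect size or formula caused this cannot be settled from the text.

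Two stronger readings should be resisted. The 8% figure is not the trial's power; it shows only that an ICC of 0.25 was not what entered the calculation. Likewise, the gap between 8% and 57% is not power lost through the label, because the label changed no n.

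**What to change.** In section 3.5:

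1. Rename Km as the coefficient of variation of the true cluster proportions within matched pairs, after confirming this against the equation actually used.
2. State the implied ICC beside it: about 0.012 at 16.4% wasting and 0.007 at 10%, with the corresponding value for the caregiver proportion. Use these, not 0.25, as the benchmark for any ICC from the mixed models.
3. Drop the claim that 0.25 is conservative unless centre-level data from the 2008 baseline survey (27 centres, 3912 children) support it on that scale.
4. Recompute the children's table from the stated rates, giving the sidedness of α and the small-sample term, or keep 180 per cluster and state the power that it delivers. If a fall to about 8% was the intended planning effect, say so and reconcile it with the stated 10%.

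The cost is a few sentences and one recalculation. Enrolment and data collection need not change. The downside is a less favourable stated power for the wasting comparison.
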